**Fig. 2 Fig2:**
[figure not shown]
Schematic overview of the follow-up timelines for the FURTHER trial illustrating the start and end of follow-up. In addition, the primary endpoint and secondary endpoint 14 days after inclusion are visualized. For all three arms, i.e., external beam radiotherapy (EBRT), magnetic resonance-guided high-intensity focused ultrasound (MR-HIFU), and EBRT + MR-HIFU, the follow-up is started after the first treatment session

Patients are free to leave the study at any time. Patients will be followed until death or end of study (6 months). To reduce the impact of patient death on loss to follow-up, the inclusion criteria “life expectancy > 3 m” was added. To further minimize missing data, patients will be actively contacted by phone on scheduled times to remind them of filling in the questionnaires. No specific dropout criteria are defined. The investigator can decide to withdraw a patient from the study for urgent medical reasons. Patients will be considered non-responders when they will be referred to alternative palliative treatments of the treated metastasis (such as (re)irradiation, radiopharmaceuticals, surgery, cryotherapy, radio-frequency ablation or nerve blocks, or MR-HIFU in the EBRT arm).

Since this study concerns a one-off treatment, patients will return to their general practitioner or referring oncologist. All participating centers have insurance that covers damage to research subjects through injury or death caused by the study. The insurance applies to damage that becomes apparent during the study or within 4 years after the end of the study.

### Study procedures

#### Radiotherapy treatment

Control patients will undergo standard radiotherapy for painful bone metastases. The radiation schedule is at the discretion of the treating radiation oncologist. The radiation oncologist may decide to administer a single fraction EBRT of 8 Gy, a multi-fraction regime of 20 Gy in 5 fractions, 24 Gy in 6 fractions, or 30 Gy in 10 fractions. Fractions are standardly delivered once daily 5 days a week, making the total treatment length variable and span multiple days for multi-fraction treatment plans. A planning CT with or without contrast agent in treatment position will be taken for target delineation. Treatment plans may be delivered using intensity-modulated radiation therapy (IMRT), volumetric modulated arc radiotherapy (VMAT), or stereotactic body radiation therapy (SBRT) technique. Plans will be accepted if at least 90% of the planning target volume (PTV) will receive 95% of the prescribed dose (V90 > 95%). Typically, a 10-mm isotropic PTV margin will be used. A maximal 3D dose of 110% will be allowed. The maximum allowed dose in organs at risk will be determined according to the local institution’s protocol. Position verification is at the discretion of the treating radiation oncologist in consultation with the clinical physicist. It is encouraged to use online position verification by use of cone beam CT at every fraction.

#### MR-HIFU treatment

MR-HIFU treatment will be delivered on a clinical MR-HIFU system (Sonalleve™ System V2, Profound Medical Corp, Mississauga, Canada, or Exablate™ 2100, Insightec, Tirat Carmel, Israel), integrated into a 1.5- or 3-T MR scanner (Achieva™, Ingenia™, Philips Healthcare, Best, The Netherlands, or Signa™, GE Healthcare, Milwaukee, WI, USA). MR-HIFU treatment will aim at ablating the periosteum followed by ablation of the bone metastasis if feasible and safe. HIFU treatment will be performed in accordance with the international consensus paper. [12]

During treatment preparation, the skin overlying the site of interest will be shaved and premedication (consisting of analgesics) will be administered. The procedure will be done using either procedural sedation and analgesia or general anesthesia. Patients will be positioned to obtain an HIFU beam path as perpendicular to the cortical bone surface as possible. After treatment planning and patient positioning, a low-energy sonication test will be performed to confirm reachability and correct for potential HIFU beam path distortion. Maintaining a temperature of at least 55 °C for 1 s as measured by MR thermometry in front of the cortical bone is considered to deliver a thermal dose high enough to achieve adequate ablation of the periosteum [36, 37]. During treatment, real-time temperature mapping will be used to monitor whether this goal was achieved and to determine the completion of treatment. Preferably full lesion surface coverage will be achieved by systematically sonicating treatment cells in a contiguous way, respecting system-recommended cooling times between sonications. After the HIFU procedure, a contrast-enhanced T1w-scan using a gadolinium-based standard MR contrast agent will be acquired to evaluate the treatment effect. The patients are then transferred to the recovery room or patient ward for medical supervision. When the patient has recovered from procedural sedation and no complications have occurred, the patient can be discharged on the same day. Alternatively, patients may, at the discretion of the treating physician, stay overnight at the hospital. The MR-HIFU treatment exists in one session, and the treatment duration is several hours, depending on lesion size and location. The MR-HIFU procedure has a good safety profile: there is a small risk of minor treatment-related side effects including pain in the treated area, first-/second-degree skin burns, and bruising. Severe side effects are extremely rare and include necrosis of nontarget tissue, ulcerating skin burns, and anesthetics-related complications [13]. These side effects will be monitored during hospitalization and follow-up phone calls. If MR-HIFU treatment does not alleviate pain within 4 weeks after treatment, patients will be offered standard care (EBRT).

#### Combined treatment

Patients allocated to the combined intervention arm will undergo both interventions as described above. In our previous research, it was shown that the combined treatment of EBRT and MR-HIFU is feasible and safe [25]. Clinical outcomes were promising and need to be further assessed in this comparative trial.

In the combination treatment arm, both treatments will be planned as soon as possible following inclusion (preferably within one week), to ensure rapid pain palliation. The pre-treatment appointments will be planned in a way that is least burdensome for the patient. Therefore, flexible planning of preoperative screening and MR-HIFU treatment to minimize extra hospital visits is encouraged. To ensure an efficient workflow for the combined arm, a weekly available MR-HIFU slot is advised. The total treatment length is defined as the time between the first and last treatment session and depends on EBRT fractionation schedule and MR-HIFU availability.

#### Analgesic medication

Patients may receive pain medication and/or dexamethasone as required by their symptoms, both before and after the EBRT and/or MR-HIFU treatment. The amount of pain medication used is part of the primary and secondary endpoints of the study and will be recorded at baseline before treatment and during follow-up. During the MR-HIFU treatment, the patient will receive hypnotic and analgesic agents under the direct supervision of an anesthesiologist or sedationist for pain control and to ensure a stable patient position during treatment. Drug selection will be based on practitioner preference.

### Sample size calculation

The study is powered to detect a difference in proportions of patients with pain response of the treated bone metastasis at 14 days after the start of treatment. For this purpose, the two MR-HIFU arms will be combined, and the sample size will be determined on a 2:1 comparison. We calculated we need 72 patients in each arm to achieve a power of 90%, using a one-sided alpha of 5% and assuming a 10% post-randomization dropout using R version 4.0.4 (R foundation for statistical computing; https://R-project.org/). We assume that the response rates during this trial will be similar to previous studies. Therefore, we base this calculation on previous research showing that the proportion of patients with successful pain palliation at 14 days following the start of treatment is 0.69 for MR-HIFU and 0.40 for EBRT [9, 14]. We conservatively assume that 10% of patients allocated to one of the MR-HIFU arms will not be able to undergo MR-HIFU and will therefore receive EBRT.

### Statistical analysis

All statistical analyses will be performed using IBM SPSS statistics, version 24 (IBM Corp. Armonk, NY, USA) and R version 4.0.4 (R foundation for statistical computing; https://R-project.org/). Data characterized by normal distribution will be expressed as means with standard deviations. Parameters not normally distributed will be expressed as medians with the interquartile ranges. Data will be analyzed according to the intention to treat and per-protocol principle. In case of post-treatment dropout (i.e., patients not surviving longer than a week, or patients unable to provide pain scores and analgesic use), a worst-case analysis will be performed, where dropped-out patients will be classified as non-responders.

The domain of the primary outcome is pain response measured by the Brief Pain Inventory (BPI [28, 29]) at baseline and 14 days following the start of treatment. Pain response is defined as a reduction of pain score ≥ 2 points without an increase of analgesic intake, or a reduction of analgesic intake of ≥ 25% without an increase of pain score at the treated site. The method of aggregation is the proportion of patients with a complete or partial pain response between baseline and 14 days following the start of treatment. Differences in pain response between arms will be compared by *χ*^2^-test. We will also conduct a time-to-event analysis for pain response. Here, the method of aggregation is the median time to pain response. Survival analysis will be performed by the Kaplan–Meier estimate and is calculated as the number of subjects surviving divided by the number of patients at risk (proportion). Survival proportions will be compared at 6 months. Toxicity will be presented as the proportion of CTCAE grade 3–4 toxicity in the 6 months following the start of treatment and differences will be tested with the *χ*^2^-test. QoL will be expressed as the mean (or median) score on a scale of 0–100 (EORTC [31–35]) and compared between the three groups at 3 and 6 months after treatment starts. A mean change of 10% of the scale breadth from the baseline will be considered a clinically relevant change in QoL. We will evaluate the pattern of QoL as a continuous outcome over time using mixed models. Differences with a *P*-value of < 0.05 will be considered statistically significant. No additional subgroup analyses are planned.

For the cost-effectiveness analysis, the primary outcome will be presented as cost per responder. Quality-adjusted life years (QALYs) will be derived from the EQ-5D-5L questionnaires to be applied in the cost-utility analysis. The costs of MR-HIFU and EBRT will be calculated using an actual cost accounting approach.

Adopting a payer perspective, we will calculate the incremental cost-effectiveness and cost-utility ratios at 6 months of follow-up. Deterministic and probabilistic (i.e., bootstrapping) sensitivity analysis will be conducted to test the robustness of the results. Because of the short timeframe, discounting will not be considered.

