**Secondary outcomes**	
2.1. Patient-reported pain scores	Assessed using the BPI and patient pain diary during the first 21 days, at 4 and 6 weeks and 3 and 6 months following treatment
2.2. Physician reported toxicity	Assessed by telephone call at 3 days; 1, 4, and 6 weeks; and 3 and 6 months following completion of treatment according to the Common Terminology Criteria for Adverse Events (CTCAE) version 5.0
2.3. Patient-reported quality of life	Assessed using the EORTC QLQ BM22, C15-PAL, EQ-5D-5L, and PGIC at baseline; 1, 2, and 4 weeks; and 3 and 6 months following completion of treatment
2.4. Local tumor control	Assessed using CT and/or MRI imaging at patient discretion at 3 and/or 6 months after completion of treatment
2.5. Levels of anxiety and depression	Assessed among patients, patients’ partners, and caregivers by the Hospital Anxiety and Depression Scale (HADS) and EDIZ-list at baseline; 1, 2, 4, and 6 weeks; and 3 and 6 months following completion of treatment
2.6. Cost-effectiveness of the treatment	Assessed as cost per responder and cost per quality-adjusted life years (QALY), from a payer perspective, at 6 months of follow-up

Pain response will be based on the numeric rating scale (NRS) and the pain severity index calculated from the Brief Pain Inventory (BPI) questionnaire [28, 29]. In addition, analgesic and anti-neuropathic drug use is recorded, and all opioid analgesics are expressed as the oral morphine equivalence dose (OMED). The primary endpoint of the trial will follow the International Consensus on Palliative Radiotherapy Endpoints for Future Clinical Trials in Bone metastases [30]. In accordance with the consensus, pain will be assessed by the worst pain score over the previous 3 days. Patients will be categorized as responders when either a reduction of pain score of at least 2 points without increase of analgesic intake is achieved, or a reduction of analgesic intake of at least 25% is accomplished without an increase of pain score at the treated site. All other patients will be categorized as non-responders.

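### The dropout rule labelled worst-case is non-responder imputation in every arm, which is not the worst case for a superiority claim, and it does not clearly reach randomised patients who never start treatment

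*Protocol article*

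**What the plan says.** The dropout rule is in the Statistical analysis section. Its scope is given as "In case of post-treatment dropout (i.e., patients not surviving longer than a week, or patients unable to provide pain scores and analgesic use"), and its content is that "a worst-case analysis will be performed, where dropped-out patients will be classified as non-responders". No distinction is made between arms. The same section states that "Data will be analyzed according to the intention to treat and per-protocol principle".

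Four other places bear on it:

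- Sample size calculation: the number of patients is set "using a one-sided alpha of 5% and assuming a 10% post-randomization dropout". That allowance is counted from randomisation, not from treatment. The section also assumes that "10% of patients allocated to one of the MR-HIFU arms will not be able to undergo MR-HIFU and will therefore receive EBRT".
- Objectives: the primary endpoint is timed at 14 days from the start of treatment. After the response criteria are given, "All other patients will be categorized as non-responders".
- Patient selection and follow-up: "Patients will be considered non-responders when they will be referred to alternative palliative treatments of the treated metastasis". No date limit is attached.
- Study design and Intervention allocation: this is a superiority trial, and neither patients nor doctors are blinded.

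**The concern.** In a superiority trial, a worst-case analysis asks whether the claimed benefit survives the least favourable values that the missing outcomes could take. Setting every missing outcome to failure answers that only for the experimental arms. In the control arm it is the most favourable choice for the new treatment. A report that MR-HIFU's advantage survived a worst-case analysis would therefore claim more than was tested.

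The design makes this more than a matter of terms. Patients know their allocation and report their own pain, so loss need not be equal across arms. If EBRT patients leave more often, the rule moves the result towards MR-HIFU.

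The second issue is scope. The rule is worded for loss after treatment. A patient who is randomised and never starts has no day 14 and, because the diary begins on the treatment day, no diary either. That patient is part of the post-randomisation allowance but is not clearly reached by the rule.

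**Working it through.** **Inputs**

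- 72 patients per arm, with the two MR-HIFU arms pooled: 144 against 72 (Sample size calculation). The 72 is taken as stated. The section's own inputs give 46 per arm before the dropout allowance and 52 after it, so 72 is more than they require. That is a separate matter and does not affect this comparison.
- Planned response rates: EBRT 0.40. For MR-HIFU, with 10% receiving EBRT, 0.9 × 0.69 + 0.1 × 0.40 = 0.621 + 0.040 = 0.661.
- Dropout: the protocol's single figure of 10%. Two assumptions are added here: it is equal in each arm, and completers respond at the planned rates.
- In whole patients: 7 of 72 and 14 of 144 missing leave 65 and 130 completers. Responders are 0.40 × 65 = 26 and 0.661 × 130 ≈ 86.

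**Formula**

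z = (p1 − p2) / √[p(1 − p)(1/n1 + 1/n2)], with p the pooled proportion. z² is the uncorrected χ² statistic.

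**Three treatments of the same data**

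| Handling of missing | MR-HIFU | EBRT | Difference | z | Two-sided p | One-sided p |
|---|---|---|---|---|---|---|
| Complete cases | 86/130 = 66.2% | 26/65 = 40.0% | 0.262 | 3.48 | 0.0005 | 0.0002 |
| Protocol rule: all missing fail | 86/144 = 59.7% | 26/72 = 36.1% | 0.236 | 3.27 | 0.001 | 0.0005 |
| Worst case: MR-HIFU missing fail, EBRT missing respond | 86/144 = 59.7% | 33/72 = 45.8% | 0.139 | 1.93 | 0.053 | 0.027 |

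For the last row: pooled p = 119/216 = 0.551; standard error = √(0.551 × 0.449 × 0.02083) = 0.0718; z = 0.1389/0.0718 = 1.93. With 15 rather than 14 MR-HIFU patients missing, the row becomes 85/144 against 33/72, with two-sided p=0.066 and one-sided p=0.033.

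In expected proportions, without rounding to whole patients:

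- Complete cases: 0.661 − 0.400 = 0.261.
- Protocol rule: 0.9 × 0.661 − 0.9 × 0.400 = 0.595 − 0.360 = 0.235.
- Worst case: 0.595 − (0.360 + 0.100) = 0.135.

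At 144 against 72, power is about 95% one-sided (91% two-sided) under the rule and about 59% (47%) under the worst case.

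**When the rule favours MR-HIFU**

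Let dE and dH be the dropout proportions in EBRT and MR-HIFU. The difference under the rule is 0.661(1 − dH) − 0.40(1 − dE) = 0.261 + 0.40·dE − 0.661·dH. It exceeds the complete-case 0.261 only if dE/dH > 0.661/0.40 = 1.65. As an illustration, 20% in EBRT and 10% in MR-HIFU give 0.595 − 0.320 = 0.275 under the rule, but 0.595 − (0.320 + 0.200) = 0.075 in the worst case. The protocol gives no dropout rate by arm, so these figures show the mechanism and are not a forecast.

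**Scope, passages side by side**

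- Dropout allowance: from randomisation (Sample size calculation).
- Dropout rule: after treatment (Statistical analysis).
- Endpoint clock: from the start of treatment (Objectives, Statistical analysis). Table 1 times it from completion, but a patient who never starts has no day 14 on either reading.
- Catch-all: everyone not meeting the response criteria is a non-responder (Objectives), with no restriction to treated patients.

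The catch-all and the intention-to-treat commitment point to counting never-treated patients as non-responders. The dropout rule's narrower wording leaves that unsaid.

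**The case against.** The strongest defence is that the rule is conservative in the protocol's own scenario. With equal dropout it shrinks the difference from 0.261 to 0.235, against MR-HIFU. At the only sidedness the protocol states, one-sided 5%, even the real worst case remains significant (p=0.027). Renaming could be called a preference, and an analysis plan that is not shown may already hold a tipping-point analysis. All of this limits the size of the point. It does not rescue the label: the document claims a property that the rule lacks, and the Statistical analysis section does not say whether its 0.05 threshold is one- or two-sided, so the worst-case result falls on either side of it.

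Three stronger readings are tempting and are not supported.

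- A reader might infer that patients lost before treatment are excluded from the intention-to-treat result, to MR-HIFU's benefit. No passage excludes them. The protocol commits to intention to treat, the Objectives catch-all makes everyone else a non-responder, and the sample size keeps patients who cannot have MR-HIFU in their arm on EBRT.
- A reader might infer a large inflation of false-positive error. With 50% true response in all arms, 20% dropout in EBRT and 5% in MR-HIFU, the one-sided error is about 27%. With 10% in each it is 5.0%, and with the split reversed it is 0.4%. The result depends entirely on rates that the document does not give.
- A reader might infer that fallback to EBRT counts as failure in the MR-HIFU arms. The alternative-treatment rule concerns a metastasis already treated, and the sample size section plans for that fallback and credits it with the EBRT response rate.

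**Conclusion.** The point holds in limited form. Non-responder imputation in every arm is wrongly called worst-case. At the planned rates with 10% missing in each arm, the gap between the rule and the real worst case is about 0.10 in the response difference (0.235 against 0.135). That is enough to move the two-sided p-value from 0.001 to 0.053, though not enough to lose one-sided significance. This rests on completers responding at the planned rates and on equal dropout, neither of which the document can guarantee. Whether the rule helps or hurts MR-HIFU in practice depends on whether the EBRT to MR-HIFU dropout ratio exceeds about 1.65, which is unknown.

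On scope, the finding is a mismatch of wording between three starting points (randomisation, start of treatment, after treatment). The handling of never-treated patients is unclear; the document does not state that they are excluded.

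**What to change.** 1. Rename the rule non-responder imputation.
2. State that it applies to every randomised patient without a day-14 outcome, including those who never start treatment. This agrees with intention to treat and with the catch-all in Objectives.
3. Add the arm-asymmetric worst case (missing MR-HIFU as non-responder, missing EBRT as responder), or a tipping-point table, as the sensitivity analysis. This step is needed because step 2 alone leaves the result sensitive to unequal dropout. State in advance the sidedness at which it will be read.
4. Reconcile the alternative-treatment rule in Patient selection and follow-up with Sample size calculation, so that it is clear how EBRT given in place of MR-HIFU, and referrals after the day-14 assessment, are counted in the endpoint.

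The cost is a few sentences and one extra table from data already collected, with no additional patients. The robustness result will look less favourable than under the present rule.

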## Background

Cancer-induced bone pain (CIBP) due to bone metastases often results in substantial deterioration of quality of life (QoL) in patients with advanced cancer [1, 2]. The mainstay of treatment of CIBP is oral analgesics (mostly opioids), in some cases stabilization or fixation surgery and in most cases external beam radiotherapy (EBRT) [3–5]. Although EBRT is a well-established treatment option, not all patients experience pain relief after this treatment. A recent systematic review has shown that approximately 45% of patients do not respond to EBRT and if patients do respond, it can take up to 6 weeks before adequate pain relief is reached. [6–8] Moreover, approximately 50% of initial responders experience recurrent pain, for which re-irradiation is only effective in 58% of patients [9, 10]. Fast and effective pain control is paramount to optimize QoL in palliative cancer care. Magnetic resonance image-guided high-intensity focused ultrasound (MR-HIFU), as an alternative or addition to EBRT, may improve pain palliation treatment in this patient population, by increasing the percentage of responders, and decreasing the time to response [11, 12].

MR-HIFU is a non-invasive treatment modality which can deliver acoustic energy to heat target tissue to ablative temperatures [11, 13]. One of many potential applications of MR-HIFU is in palliative pain treatment for CIBP, in which the pain palliation mechanism is hypothesized to be through ablation of periosteal nerves and tumor debulking. Previous studies have shown that pain response may occur within 3 days after MR-HIFU treatment, and response rates are promising with pain responses ranging from 67 to 88% of patients [14–21]. Moreover, combining MR-HIFU with EBRT may have a complementary or even synergistic effect on pain response [22–25]. In an earlier study, the feasibility of combined treatment was proven. [25]

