## Discussion

In this report, we present the rationale and design of the FURTHER trial. The aim of this international three-armed randomized controlled trial is to evaluate the effectiveness and cost-effectiveness of MR-HIFU—alone or in combination with EBRT—compared to EBRT as a palliative treatment option to relieve CIBP. Although the standard of care EBRT is a well-established treatment option, only approximately 55% of patients experience adequate pain relief after treatment [6]. MR-HIFU may improve pain palliation treatment for patients with painful bone metastasis, by providing fast and durable pain response in a higher percentage of patients [14]. Effectiveness and safety of MR-HIFU (alone or in combination with EBRT) as first-line treatment have never been compared to EBRT alone in an RCT.

MR-HIFU treatment provides a non-invasive, radiation-free treatment option for patients with CIBP caused by bone metastases. The treatment can be done in a single session and can be repeated multiple times if necessary. Preliminary clinical studies on the use of MR-HIFU for palliation of painful bone metastases demonstrated excellent response rates and safety [13–21]. Hurwitz et al. (2014) reported results of a multicenter randomized placebo-controlled trial to evaluate the safety and efficacy of MR-HIFU for treating bone metastases that were painful despite the previous radiotherapy, were unsuitable for radiotherapy, or who declined radiotherapy [14, 38]. Response to MR-HIFU was rapid, with about two-thirds of patients reporting pain response within a few days after treatment. Lee et al. (2017) performed a single-center matched-pair study which showed that MR-HIFU provides a similar overall treatment response rate but faster pain relief compared to EBRT and thus has the potential to serve as the first-line treatment for painful bone metastasis in selected patients [18]. Harding et al. (2018) evaluated QoL after MR-HIFU for painful bone metastasis and showed that there was a substantial positive effect on physical functioning and symptoms .[39]

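### The median chosen to summarise time to pain response sits just under the EBRT response plateau, so in that arm it will usually lack an upper confidence limit and may not be reached

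*Protocol article*

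**What the plan says.** After the primary comparison of proportions, the Statistical analysis section adds a second look at the same outcome: "We will also conduct a time-to-event analysis for pain response". Its summary is then fixed: "Here, the method of aggregation is the median time to pain response". The Objectives section includes time to pain palliation among the features to be compared between the MR-HIFU and EBRT groups.

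The expected EBRT response appears in three places:

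- Background: "approximately 45% of patients do not respond to EBRT and if patients do respond, it can take up to 6 weeks".
- Discussion: "only approximately 55% of patients experience adequate pain relief after treatment".
- Sample size calculation: the day-14 response "is 0.69 for MR-HIFU and 0.40 for EBRT".

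The planned size is "72 patients in each arm to achieve a power of 90%, using a one-sided alpha of 5% and assuming a 10% post-randomization dropout". Pain is recorded daily to day 21 and after that only at scheduled visits (4 and 6 weeks, 3 and 6 months). Follow-up ends at death or 6 months.

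**The concern.** A median time to response exists only if at least half the arm responds, and it is precise only if the curve goes well past one half. With an EBRT plateau near 55%, the median is the time by which 0.50/0.55 = 91% of eventual responders have responded. It then depends mainly on whether slightly more or slightly fewer than half the arm ever responds, and says little about how quickly responders respond.

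Speed is a main part of the case for MR-HIFU: the Objectives section contrasts an effect within days with one that takes weeks. If the control-arm median has no upper limit, or is missing, the contrast of medians cannot be given a usable interval. This is a stated choice of summary that fits poorly with the protocol's own figures. It is not a detail left to a later document.

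**Working it through.** The protocol gives no figure for the time-to-response analysis, so there is none to reproduce. The arm size of 72 is taken as planned.

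**Inputs from the protocol.** n = 72 per arm, EBRT response 0.40 by day 14 and about 0.55 overall, dropout 10% (Sample size calculation, Background, Discussion).

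**Assumptions.** The overall figure is read as the proportion who ever respond, reached by day 42. Because the protocol does not define it, 0.60 and 0.65 are also shown.

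**Step 1: is the median reached?** With X ~ Binomial(72, p) responders, the median is not reached if X ≤ 35. At p = 0.55 the expected number is 72 × 0.55 = 39.6.

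**Step 2: does the 95% upper limit exist?** At the plateau the proportion without response is S = 1 − X/72. The upper confidence limit of S must fall to 0.50 or below.

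- Plain limits: S + 1.96·√(S(1−S)/72) ≤ 0.50. With X = 44, S = 0.389 and the limit is 0.501, which fails. With X = 45, S = 0.375 and the limit is 0.487, which passes. So 45 responders (62.5%) are needed.
- Log-log limits: with X = 44 the limit is 0.499, so 44 responders (61.1%) are needed.

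Both thresholds exceed the 39.6 expected.

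| Ever-response in EBRT | Median not reached | No upper limit (log-log) | No upper limit (plain) |
|---|---|---|---|
| 0.55 | 16.6% | 82.2% | 87.8% |
| 0.60 | 3.3% | 52.6% | 62.0% |
| 0.65 | 0.3% | 20.6% | 28.2% |

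**Step 3: dropout.** Kaplan–Meier curves were simulated at a 0.55 plateau on the protocol's assessment schedule, with 10% dropout by 6 weeks. The median was not reached in about 20–23% of trials if dropouts are censored, and in about 26–30% if they stay in as non-responders. Overall that is roughly 20–30%.

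**Step 4: the visit schedule.** Suppose response accrues linearly to 40% at day 14 and then to 55% at day 42. Expected response is 43.75% at day 21 and 47.5% at day 28. The EBRT median then falls within the daily-diary window in 17% of trials, on the day-28 or day-42 visit in 66%, and is not reached in 17%. Where it exists, it is usually a visit date.

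**Step 5: the MR-HIFU arms.** Allowing for the 10% who receive EBRT instead, day-14 response is 0.9 × 0.69 + 0.1 × 0.40 = 0.661. With an assumed plateau of 0.70, the median is essentially always reached, at about day 11. The upper limit is missing in 3–9% of trials for a single arm and in under 1% for the two arms pooled.

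**Step 6: precision of a fixed-day summary.** At day 14, EBRT gives 0.40 ± 1.96·√(0.40 × 0.60/72) = 0.40 ± 0.113. The pooled MR-HIFU arms give 0.661 ± 1.96·√(0.661 × 0.339/144) = 0.661 ± 0.077. The difference is 0.261, with a 95% interval of about 0.12 to 0.40. Such an estimate is always available.

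**The case against.** The strongest reply is that early benefit is already measured elsewhere. The primary endpoint was set at day 14 because MR-HIFU is expected to act fast, the trial is powered on it, and that proportion can always be estimated. Time to response is an added analysis without its own row in Table 1. A reader might infer that the trial cannot put a figure on the benefit it was built to show. For the reason just given, the documents do not support that.

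A reader might also infer that reaching the EBRT median is a coin toss. If every one of the 10% dropouts never responds, the plateau is 0.9 × 0.55 = 0.495 and the median is missing in 49% of trials. But the protocol does not say that its worst-case dropout rule applies to this analysis, and dropouts spread over 6 weeks give the lower figures above. At 55% without dropout, the point estimate is available in about 83% of trials.

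The 55% is itself a literature figure with no stated definition or time point. First response at any time, caught by daily diaries, could well be higher. This stands, and is why the range to 65% is shown.

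It is also tempting to say that the Kaplan–Meier method mishandles deaths here. The protocol names that method only for survival. Under an assumed 30% mortality at 6 months, censoring deaths would change the day-42 response only from 0.537 to 0.550, about 1 point.

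Finally, an analysis plan that is not shown may add a log-rank test or a hazard ratio, and naming the median does not exclude these. That is fair. They would compare the curves, but would not repair the summary that this document does state.

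**Conclusion.** The point holds as a minor one. The stated summary is a poor match for the protocol's own EBRT figures. At 72 per arm and 55% ever-response, the EBRT median will usually lack a 95% upper limit and will be missing altogether in a minority of trials. That rests on reading the 55% as the ever-response plateau. At 60–65% the missing median almost disappears, while the missing upper limit remains common. Only the EBRT arm is affected. The consequence is a secondary speed comparison that may have no usable interval. The primary analysis is untouched.

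**What to change.** In the Statistical analysis section, replace the median as the main summary of time to pain response by the cumulative incidence of first pain response in each arm, with death and referral to alternative palliative treatment as competing events. Report between-arm differences with confidence intervals at days 3, 7 and 14, from the daily diary, and at week 4, from the scheduled visit (the daily entries stop at day 21). Give the median descriptively where it is reached.

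The cost is a change of wording and slightly more analysis work; no new data are needed. One drawback is that the day-14 contrast partly overlaps the primary endpoint. Cumulative incidence in all patients also still mixes speed with the final level of response, though the early days bear mostly on speed.
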